### Objectives and endpoints

Primary objective is to determine the safety and efficacy of the long-term administration of immunonutrients, and assessment of the patients' nutritional and physiological status as well as quality of life, while waiting for a graft. Secondary Objective is to investigate the effects of immunonutrition on post-transplant morbidities.

### Trial design and schedule (Fig. 1)

**Figure 1 F1:**
[figure not shown]
**Scheme depicting the workflow of the study**. Each subject will be recruited on the day of registration on the waiting list for liver transplantation after giving informed consent. Study nutrition ends on the day of transplantation. Subjects are randomized to two parallel groups treated for study or control product. Furthermore, patients will be followed for 12 weeks after transplantation.

Site number, patients' randomization number and initials, all demographic data (date of birth, sex, height, weight), medical history (including a complete dietary history and MELD score), physical examination, comorbidities, and concomitant medications are documented on day one. Furthermore, anthropometric, physiologic, and biochemical measurements are carried out and documented. The aforementioned measurements are performed during monthly visits until transplantation. The patients consume either the study product (ORAL IMPACT^®^) (Table 2) or control product (IMPACT-control supplement) (Table 2) once a day for the period of waiting until a graft is available. During each visit, the following data are recorded in the electronic case report form (eCRF):

**Table 2 T2:** Composition of ORAL IMPACT^® †^and IMPACT Control supplement (in powder form)

Content (1 Sachet)		**ORAL IMPACT^® ^**(74 g)	**IMPACT Control **(74 g)
-Protein	g	16.7	13.0
-Casein/Whey	g	(13)	(13)
-L Arginine	g	(3.74)	-
-Fat	g	8.3	8.3
-Essential FA (LA+LNA)	g	(0.94)	(2.6)
-n-6-FA (LA)	g	(0.74)	(2.6)
-n-3FA (EPA+DHA+LNA)	g	(1)	-
Carbohydrates	g	40.2	43.94
Fibres	g	3	3
RNA	mg	390	-
Energy	g	302.8	302.8
-kcal/ml		§	§
-P:F:C	%	22:25:53	17:25:58
Sodium	mg	320	320
Potassium	mg	402	402
Calcium	mg	240	240
Magnesium	mg	80	80
Phosphorus	mg	216	216
Chloride	mg	480	480
Iron	mg	3.6	3.6
Copper	mg	0.5	0.5
Manganese	mg	0.6	0.6
Zinc	mg	4.5	4.5
Fluoride	mg	0.5	0.5
Iodine	mcg	45	45
Chromium	mcg	30	30
Molybdenum	mcg	60	60
Selenium	mcg	14	14
Retinol (Vit. A.)	mg	0.3	0.3
Calciferol (Vit. D)	mcg	2	2
Tocopherol (Vit. E)	mg	4	4
Phyllochin. (Vit. K1)	mg	20	20
Thiamine (Vit. B1)	mg	0.36	0.36
Riboflavine (Vit. B2)	mg	0.52	0.52
Pyridoxine (Vit. B6)	mg	0.44	0.44
Cyanocobal. (Vit. B12)	mcg	1.2	1.2
Ascorbic Acid (Vit. C)	mg	20	20
Biotin	mcg	30	30
Folic Acid	mcg	60	60
Niacinamide	mg	4.8	4.8
Pantothenic Acid	mg	2.4	2.4

^†^; IMPACT^® ^is a food for special medical purpose (FSMP)

§ content of sachet to be dissolved in 250 ml water for each serving

FA; fatty acid, LA; linoleic acid, LNA; linolenic acid, EPA; Eicosapentaenoic acid, DHA; docosahexaenoic acid, RNA; ribonucleic acid, kcal; kilocalorie, ml; millilitre, P:F:C; protein:fat: carbohydrate, Vit.; vitamin.

Reference:

A. Anthropometric measurements, including:

• Body weight (BW, kg),

• Body mass index (BMI),

• Mid-arm muscle area (MAMA, cm2)

• Mid-arm circumference (MAC, cm),

• Mid-arm muscle circumference (MAMC (cm) = MAC (cm) - [0.314 × TSF (mm)]),

• Triceps skinfold thickness (TSF, mm),

• Lean body mass (LBM, kg), and

• Creatinine height index (CHI, %) from 24-hour urinary creatinine excretion (patients are advised to collect their urine for 24 hours right before each monthly visit and bring it to the center with them)

B. Biochemical parameters, including albumin, bilirubin, creatinine, urea, alkaline phosphatase, transaminases (ALT, AST), INR, phosphate, transferrin, total body potassium)

C. Endocrine measurements, including fasting insulin, GH, and IGF-1

D. Resting energy expenditure (REE, kcal/d) by indirect calorimetry

E. Voluntary muscle function: grip strength (kg)

F. Respiratory function: Peak expiratory flow rates

G. Fatigue score and HRQL (SF-36 questionnaires [24]).

During each monthly visit, patients will be provided with the required monthly amount of study product (or control product) and are asked to return the emptied study boxes with them to the next monthly session to warrant that they are compliant with the trial regimen. Further, between the two consecutive monthly visits, the trial investigator has to phone call the patient weekly to check for both compliance and adverse events. Deviations of the protocol are documented in the eCRF. The trial ends on the day a graft becomes available. A patient consuming a total of 80% of the calories prescribed over the entire preoperative study period is considered a "completer". Post-transplant investigations concern anabolic recovery after transplantation as shown by:

• post-transplant mechanical ventilation

• total hospital stay

• wound healing

• infectious morbidities (pneumonia, intraabdominal abscess, sepsis, central line sepsis, wound infection, and urinary tract infection)

• CRP levels

• acute and chronic rejection, and

• mortality (ICU mortality, hospital mortality, 28-day mortality, and survival at the 12^th ^week post-transplant surveillance period).

These post-transplant parameters are investigated and documented during the patients' posttransplant hospital stay daily and further until the 12^th ^week posttransplant through postoperative follow-up sessions. Sepsis is defined as the presence of at least 2 out of the following 4 criteria: (1) temperature >38°C or <36°C, (2) tachycardia >90/min, (3) leukocytosis >12/nl or leukopenia <4/nl, and (4) respiratory insufficiency (any of the 3 following criteria: respiratory rate >20/min, hyperventilation with PaCO_2 _<32 mmHg or PaO_2 _<70 mmHg (spontaneous breathing) or PaO_2_/FiO_2 _<175 mmHg (mechanical ventilation) [25]. CRP will be measured weekly posttransplant until the patient is discharged, and then along with other investigations through postoperative follow-up sessions. During the posttransplant phase, subjects will routinely receive immunosuppressive therapy which includes cyclosporine A, mycophenolate (Myfortic^®^) and steroids. The immunosuppression will be done with or without induction therapy [Simulect^® ^(Basiliximab)].

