### Statistics and data management

All analyses will be carried out on an "intent-to-treat" basis. However, attempts will be made to analyze "per protocol", "completer", and "intent-to-treat" populations separately, when statistically appropriate. Repeated-measures analysis of variance (ANOVA) will be used followed by t-test when significant differences are detected by ANOVA. Pearson Chi-square test or Fisher's exact test will be used when appropriate. Times to an event are described by Kaplan-Meier and compared between groups by the log-rank test. The differences of the analysis variables are tested with the paired t-test or, in case of uneven distribution, the Wilcoxon-test (2-sided) for within group comparison. The Mann-Whitney U test will be used to detect differences between study groups. The following statistical values will be calculated where appropriate: mean, standard deviation, 95%-confidence interval of the mean, minimum, lower quartile, median, upper quartile, maximum, valid number, frequency count, and percentage. The laboratory values will be counted according to their normal ranges (below normal, normal, and above normal). Biometric analysis will be defined in the statistical analysis plan which has to be authorized before unblinding by the biometrician, the sponsor, and the principal investigator. One interim analysis will be performed after half of the patients have finished the clinical period for the primary endpoints.

All patient data (clinical and resource use) generated during the study will be recorded on the eCRFs specifically designed to meet the data recording requirements of the clinical study protocol provided by HealthEcon AG. All data management activities will be done according to ICH-GCP guidelines. Responsibility for data management is with HealthEcon AG, Basel, Switzerland. Throughout the study, all patient information in the eCRF will only be identifiable by means of an identification number (patient number) and possibly patient initials.

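### Mortality and the secondary morbidity outcomes are defined only after transplantation, so waiting-list death is no named outcome and these comparisons are conditional on receiving a graft

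*Protocol article*

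**What the plan says.** **When exposure starts and stops.** The Abstract and Subject recruitment place enrolment on the day of listing and end study nutrition on the day of transplantation. Trial design and schedule adds: "The trial ends on the day a graft becomes available". No end of follow-up is given for a patient who never receives a graft.

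**Objectives.** Under Objectives and endpoints, "Primary objective is to determine the safety and efficacy of the long-term administration of immunonutrients", with status assessed during the wait. "Secondary Objective is to investigate the effects of immunonutrition on post-transplant morbidities".

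**Where mortality sits.** Trial design and schedule opens its outcome list with "Post-transplant investigations concern anabolic recovery after transplantation as shown by". The list covers ventilation, hospital stay, wound healing, infections, CRP and rejection, and ends with "mortality (ICU mortality, hospital mortality, 28-day mortality, and survival at the" 12th post-transplant week. The collection window follows: "These post-transplant parameters are investigated and documented during the patients' posttransplant hospital stay daily", then follow-up sessions to week 12.

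**Safety recording.** Adverse events says that all adverse events are recorded. It then exempts events related to the diagnosis that led to listing from being noted as AE or SAE, unless the investigator attributes them to the product. The SAE form is required for SAEs potentially associated with the product.

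**Analysis.** Statistics and data management says "All analyses will be carried out on an 'intent-to-treat' basis" and "Times to an event are described by Kaplan-Meier and compared between groups by the log-rank test". It names neither an event nor a time origin.

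**The concern.** The product can affect survival directly only while it is being taken, and that is the period in which no mortality outcome is defined. All four mortality measures start at an event that occurs after randomisation and may itself depend on treatment.

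Two things are at stake. The first is omission: a difference between arms in waiting-list death, in either direction, is not a planned comparison, although safety during the wait belongs to the primary objective. The second is selection: if the arms lose different patients on the list, the transplanted groups are no longer the groups that randomisation made comparable. A difference in post-transplant mortality, infection or rejection could then reflect who reached surgery.

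Safety reporting does not clearly close the gap. In end-stage liver disease, a death from liver failure on the list is an event related to the initial diagnosis. Under the exemption it may reach neither the SAE form nor the safety board.

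**Working it through.** **Figures in the document.** None bears on waiting-list death, delisting or post-transplant mortality. The sample size concerns the mid-arm muscle area rate and is not in dispute. With SD 0.21 and difference 0.1% per day, 80% power and two-sided 0.05, a t-based calculation gives 70.2, so 71 per group as stated. Then 71 × 1.10 = 78.1, matching the stated 78 per group and 156 in total. I use 78 and 156 only as denominators. All rates below are assumptions.

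**1. Patients left for post-transplant outcomes.** With a fraction f never transplanted, 156 × (1 − f) remain:

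| f | remaining |
|---|---|
| 5% | 148 |
| 10% | 140 |
| 20% | 125 |
| 30% | 109 |

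**2. Omission.** Let w be the risk of death on the list and p the risk of death by 12 weeks after transplantation. For simplicity, every survivor of the wait is transplanted. Mortality from randomisation is w + (1 − w) × p.

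- Product, w = 0.10, p = 0.10: 0.10 + 0.90 × 0.10 = 0.19.
- Control, w = 0.20, p = 0.10: 0.20 + 0.80 × 0.10 = 0.28.

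The planned measure reports p alone, 10% v 10%. This example shows omission only: the post-transplant comparison is not distorted, because p was set equal.

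**3. Selection.** Suppose patients who survive the wait on either product have 8% post-transplant mortality, and those who survive it only on the study product have 30%. Write w_C and w_P for waiting-list death in the control and product arms.

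- Post-transplant mortality, product: [(1 − w_C) × 0.08 + (w_C − w_P) × 0.30] / (1 − w_P). Control: 0.08.
- From randomisation, product: w_P + (1 − w_C) × 0.08 + (w_C − w_P) × 0.30. Control: w_C + (1 − w_C) × 0.08.

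With w_C = 0.20 and w_P = 0.10:

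- post-transplant, product: (0.064 + 0.030) / 0.90 = 10.4%, against 8.0% in control;
- from randomisation, product: 0.10 + 0.094 = 19.4%; control: 0.20 + 0.064 = 26.4%.

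With w_C = 0.10 and w_P = 0.05:

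- post-transplant, product: (0.072 + 0.015) / 0.95 = 9.2%, against 8.0%;
- from randomisation, product: 0.05 + 0.087 = 13.7%; control: 0.10 + 0.072 = 17.2%.

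In both cases the product looks worse after transplantation and better from randomisation. With w_C = w_P the formulas give 8% in both arms, so the reversal needs an effect of treatment on who survives the wait.

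**4. Precision.** For 19% v 28% with 78 per arm, the standard error of the difference is √(0.19 × 0.81/78 + 0.28 × 0.72/78) = √(0.00197 + 0.00258) ≈ 0.067. The 95% interval is about ±13 percentage points around a 9-point difference.

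**The case against.** The strongest reply is that post-transplant morbidity is openly the secondary objective, that mortality is one item in its list and did not drive the sample size, and that the primary comparison does not depend on it. This stands. The primary endpoints are measured at day one and monthly until transplantation, and need no graft.

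Four stronger readings are tempting and should not be drawn:

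- *The whole intention-to-treat analysis is confined to transplanted patients.* No text says so. The conditioning arises only for outcomes that cannot be observed without a graft, and for mortality because of where it is defined.
- *Morbidity during the wait goes uncounted, or a survival effect could not come to light.* Adverse events are recorded, investigators telephone weekly and an independent safety board monitors SAE reports. The exemption supports possible under-capture. What can be said is that waiting-list survival is not a planned comparison. The Conclusion mentions survival, but it is unclear whether post-transplant survival alone is meant.
- *Deaths are censored in Kaplan-Meier analyses of discharge or extubation.* The article states no such rule and does not say that these are time-to-event outcomes. That detail belongs to an analysis plan not shown.
- *The worked examples demonstrate bias in this trial.* They rest on assumed rates. They show what the definition would miss or could reverse.

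It can also be said that the analysis plan, or the full protocol behind the article, may deal with this. That holds for analytic detail, but the outcome list, its collection window and the exemption are stated here, and all four mortality measures are explicitly placed after transplantation.

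**Conclusion.** The point holds for mortality and the post-transplant outcomes, and only for those. As written, the plan compares mortality among patients selected by an event after randomisation, calls every analysis intention-to-treat, and names no outcome for death or delisting while the product is taken.

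The size cannot be derived from the document. Under the assumed rates, a 9-point difference from randomisation (19% v 28%) shows as none, and differences of 7.0 points (19.4% v 26.4%) or 3.5 points (13.7% v 17.2%) in favour of the product show as 2.4 or 1.2 points against it. The reversal requires both that treatment changes waiting-list survival and that the extra survivors carry higher surgical risk. If treatment does not change who reaches a graft, no bias arises by this route, but the label is still inaccurate.

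The trial is too small to settle mortality either way. The case for the change is complete and unselected safety reporting, not a powered survival test. It should be made. It leaves the primary comparison and the sample size untouched.

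**What to change.** 1. Add all-cause death from randomisation in all randomised patients, counted to 12 weeks after transplantation, or to a stated study end for those never transplanted. Analyse it by assigned arm and report an estimate with its interval.
2. Record every death and delisting on the waiting list regardless of attribution, outside the adverse-event exemption. Report them by arm as cumulative incidence, with transplantation as the competing event.
3. Keep the existing post-transplant outcomes, but label them 'among transplanted patients' and not intention-to-treat. State beside them how many of those randomised in each arm were transplanted.

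The cost is modest but more than wording. A follow-up end date must be set, and vital status recorded up to it, for patients who are never transplanted. The planned weekly calls and monthly visits cover the wait itself, but the article describes no contact after delisting, so that part needs a new recording rule.

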### Sample size calculation

The sample size calculation is based on the detection of significant differences in MAMA, one of the primary endpoint parameters of this trial. A clinical trial on enteral hyperalimentation in malnourished patients with cirrhosis and ascites [26] was used as an exemplary model. The rate was measured in percent per day, i.e. MAMA changes divided by number of days between admission and discharge. After eliminating the gross outlier of this study, the standard deviation of this rate was 0.21% per day. The clinically relevant difference was set to 0.1% MAMA per day. Therefore, the sample size necessary for the trial with a power of 80% and a two-sided significance level of 0.05 was calculated to be 71 patients per group. An assumed 10% drop-out rate in this trial (due to non-compliance, intolerance, premature discontinuation, etc) will raise the sample size to 78 patients per group. Therefore, at least a total of 156 patients have to be included to the trial in order to yield 142 completers.

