## Conclusion

This randomized controlled trial is intended to investigate the long-term preoperative effects of ORAL IMPACT^® ^on the nutritional status as well as the outcome of the patients with ESLD listed for transplantation. The working hypothesis is that Oral IMPACT^® ^has the ability to downregulate the inflammatory responses to chronic disease and surgery through immune modulation. Safety and efficacy, anthropometric and physiological parameters, HRQL, as well as post-transplant morbidities and survival will be assessed.

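### Sepsis is counted as an infectious morbidity but defined by two of four inflammatory or respiratory signs, with no infection required, so that component can dilute or misattribute a treatment difference

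*Protocol article*

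**What the plan says.** In the protocol article, the section Trial design and schedule lists the post-transplant outcomes. One of the seven groups is "infectious morbidities (pneumonia, intraabdominal abscess, sepsis, central line sepsis, wound infection, and urinary tract infection"). The Abstract (Methods/design) also places sepsis among the infectious morbidities.

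Later in the same section comes the operational rule: "Sepsis is defined as the presence of at least 2 out of the following 4 criteria". The first three criteria read "1) temperature >38°C or <36°C, (2) tachycardia >90/min, (3) leukocytosis >12/nl or leukopenia <4/nl", and the last begins "4) respiratory insufficiency (any of the 3 following criteria: respiratory rate >20/min". The respiratory criterion can also be met by a low PaCO2, by a low PaO2 in spontaneous breathing, or by a low PaO2/FiO2 ratio under mechanical ventilation.

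On timing, the section says "These post-transplant parameters are investigated and documented during the patients' posttransplant hospital stay daily", with follow-up sessions to week 12 after discharge.

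Two other statements bear on the point. Objectives and endpoints says "Secondary Objective is to investigate the effects of immunonutrition on post-transplant morbidities", so the outcome is secondary. The Conclusion gives the working hypothesis that the product "has the ability to downregulate the inflammatory responses to chronic disease and surgery through immune modulation".

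**The concern.** The label and the rule do not match. The label says infection. The rule detects physiological signs that infection can cause, but so can major surgery, mechanical ventilation and the routine steroids and mycophenolate that the same section describes. As printed, a patient with a raised heart rate and a raised leukocyte count is septic, whether or not anyone suspects an infection.

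Two errors can follow, and they need not point the same way:

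- **Dilution.** If uninfected patients meet the rule equally often in both arms, they add the same kind of noise to each arm, and a true difference in infection-related sepsis shrinks.
- **Misattribution.** If the product lowers inflammatory signs, as the Conclusion hypothesises, the arms can differ on this rule while their infection rates are the same. The result would be reported as fewer infections.

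A reader of the results could not tell which had happened.

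**Working it through.** **The plan's own figure.** The only sample size derived is for mid-arm muscle area (Sample size calculation): "the standard deviation of this rate was 0.21% per day", a difference of 0.1% per day, 80% power, two-sided 5% level, 71 per group. The normal approximation gives n = 2 × [0.21 × (1.960 + 0.842) / 0.1]², which rounds up to 70. The t-test version gives 70.2, so 71, with power 0.804. The stated figure reproduces and does not depend on sepsis. No rate, effect or power is given for sepsis or for any infection.

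**Does any criterion require infection?** Temperature: no. Heart rate: no. Leukocyte count: no. Respiratory insufficiency: no; respiratory rate alone is enough. No culture, imaging, source, treatment decision, duration or exclusion of the early postoperative days is stated.

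**Dilution (all rates are assumptions).** Let s be the true risk of infection-related sepsis in an arm. Let q be the share of uninfected patients who meet two of four signs, equal in both arms. Assume every patient with true sepsis meets the rule. Then:

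- recorded risk = s + (1 − s) × q
- recorded difference = (s₁ − s₂) × (1 − q)

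Power is for a two-sided 5% comparison of two proportions with n = 71 per arm: Φ{[d − 1.96 × √(2p̄(1 − p̄)/n)] / √([p₁(1 − p₁) + p₂(1 − p₂)]/n)}, where d = p₁ − p₂ and p̄ is their mean.

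Example, s = 30% v 10% and q = 0.2:

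- p₁ = 0.30 + 0.70 × 0.2 = 0.44; p₂ = 0.10 + 0.90 × 0.2 = 0.28; p̄ = 0.36
- the two standard errors are 0.0806 and 0.0794
- (0.16 − 1.96 × 0.0806) / 0.0794 ≈ 0.03, so power is about 51%

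| True sepsis | q | Recorded | Power |
|---|---|---|---|
| 30% v 10% | 0 | 30% v 10% | 85% |
| 30% v 10% | 0.2 | 44% v 28% | 51% |
| 30% v 10% | 0.5 | 65% v 55% | 23% |
| 30% v 10% | 0.8 | 86% v 82% | about 10% (9.5%) |
| 30% v 15% | 0 | 30% v 15% | 57% |
| 30% v 15% | 0.4 | 58% v 49% | 19% |
| 30% v 15% | 0.8 | 86% v 83% | 7% |
| 40% v 20% | 0 | 40% v 20% | 74% |
| 40% v 20% | 0.4 | 64% v 52% | 30% |
| 40% v 20% | 0.8 | 88% v 84% | 10% |

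**How large might q be?** The document does not say. If an uninfected patient has probability p of meeting two signs on a given day, and days are independent, the chance of qualifying at least once in an assumed 14-day stay is 1 − (1 − p)¹⁴. This gives 25% at p = 0.02, 51% at 0.05, 77% at 0.10 and 96% at 0.20. Signs cluster within patients, so at the same daily rate the independence formula overstates how many ever qualify. It also assumes that a single qualifying day makes a case, which the text permits but does not state.

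**Misattribution.** Let true sepsis be the same, s, in both arms and let q differ. The recorded difference is (1 − s) × (q₁ − q₂). With assumed s = 20% and q = 50% v 30%, the record shows 60% v 44%: a gap of 0.8 × 0.2 = 16 percentage points with no difference in infection.

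**The case against.** The strongest reply is that the harm is narrow and unmeasured.

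- **One component of six.** The rule is stated for sepsis only. Pneumonia, intraabdominal abscess, central line sepsis, wound infection and urinary tract infection are not tied to it, and no composite of the six is defined. A reader might infer that the whole infectious outcome cannot separate the arms. The document does not support that. This part of the objection stands.
- **Assumed rates.** A reader might also infer that most transplanted patients would be recorded as septic. That is plausible under some of the daily rates above and not under others, and the document gives none. The 85% starting power rests on an assumed threefold difference; at 30% v 15%, power is only 57% with a perfect definition. Much of the weakness of this outcome may therefore have nothing to do with the definition. This stands too.
- **A condensed article.** The rule carries a citation, and the full protocol or eCRF guidance, neither of which is shown, may apply the signs only to infected patients. This lowers certainty about what would happen in practice. It does not remove the point, because the article did not leave sepsis undefined. It printed a complete rule with thresholds and no infection condition.

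**Conclusion.** The definition is wrong as written and should be corrected. It is a limited defect, affecting the sepsis component of a secondary objective and any count that includes that component. The primary endpoints and the sample size of 71 per group are untouched.

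That uninfected patients can be classified as infectious cases follows from the text alone. How much this matters does not: every power figure above depends on assumed true rates, an assumed q and, for dilution, equal q in both arms. Under the 30% v 10% assumption, even q = 0.2 takes power from 85% to 51%, so a material loss does not require an extreme value. The direction of the error is not fixed either. Dilution towards no difference is one possibility; under the trial's own hypothesis, an apparent infection benefit without one is another.

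**What to change.** Define the sepsis endpoint as at least two of the four listed criteria together with a documented or clinically suspected infection, linked to the infection data already recorded in the eCRF. Fix the wording before unblinding, in the statistical analysis plan that Statistics and data management says must be authorised by then. Report patients who meet two of four criteria without infection separately, as a systemic inflammatory response, outside the infectious morbidity count. That keeps the information relevant to the inflammatory hypothesis without calling it infection.

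The cost is one amended definition and one added eCRF item. Fewer events will be labelled sepsis, so the component will be rarer but will mean what its label says. No separate adjudication panel is needed.
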